## Abstract

**Background:**

Information technology-based methods such as bar code-assisted medication administration (BCMA) systems have the potential to reduce medication administration errors (MAEs) in hospitalized patients. In practice, however, systems are often not used as intended, leading to workarounds. Workarounds may result in MAEs that may harm patients.

**Objective:**

The primary aim is to study the association of workarounds with MAEs in the BCMA process. Second, we will determine the frequency and type of workarounds and MAEs and explore the potential risk factors (determinants) for workarounds.

**Methods:**

This is a multicenter prospective study on internal medicine and surgical wards of 4 Dutch hospitals using BCMA systems to administer medication. We will include a total of 6000 individual drug administrations using direct observation to collect data.

**Results:**

The project was funded in 2014 and enrollment was completed at the end of 2016. Data analysis is under way and the first results are expected to be submitted for publication at the end of 2017.

**Conclusions:**

If an association between workarounds and MAEs is established, this information can be used to reduce the frequency of MAEs. Information on determinants of workarounds can aid in a focused approach to reduce workarounds and thus increase patient safety.

**Trial Registration:**

Netherlands Trial Register NTR4355; http://www.trialregister.nl/trialreg/admin/rctview.asp?TC=4355 (Archived by WebCite at http://www.webcitation.org/6pqTLxc6i).

## Introduction

Minimizing the risks of prescribing and medication administration is important to enhance patient safety in hospitals [1-6]. Many hospitals have implemented information technology-based systems such as computerized physician order entry (CPOE) systems to reduce prescribing errors [7-10]. Some have also implemented electronic bar code-assisted medication administration (BCMA) systems to reduce medication administration errors (MAEs) [11-18]. BCMA systems are designed to contribute to patient safety through scanning of the bar code on the medication package and the bar code on the patient’s identification wristband to guarantee the 5 “rights” in patient medication administration: right patient, right medication, right dose, right route, and the right time. However, in practice, BCMA systems are not always used as intended, and so-called workaround occurs [19-23]. Kobayashi et al [24] defined workarounds as “informal temporary practices for handling exceptions to normal workflow.” Investigating the use of CPOE systems in hospitals, Niazkhani et al [25] described 42 types of workarounds. Koppel et al [26] documented 15 types of workarounds in the BCMA process, including affixing patients’ identification bar codes to computer carts and carrying several patients’ prescanned medications on carts. That study documented 31 roots of these workarounds. Research on workarounds in the BCMA process focused on the qualitative description of the extent and type of workarounds in the BCMA process [27,28]. Little research has been done to quantify the frequency of workarounds in the BCMA process and investigate the impact of workarounds on patient safety, in particular, MAEs as a potential consequence of workarounds. Furthermore, little is known about the potential risk factors leading to workarounds. Therefore, we designed a study aimed at determining the association of workarounds with MAEs. Our secondary objectives are to determine the frequency and type of workarounds and the frequency and type of MAE, and to identify potential risk factors for workarounds.

## Methods

### Design

This study is a multicenter prospective observational study in adult patients who are admitted to a participating hospital in the Netherlands and who have their medication administered by BCMA systems.

The regional medical ethics committee (Regionale Medisch Ethische Commissie Zorgpartners Friesland) approved the study protocol. Study data are coded to guarantee the privacy of the participants.

### Setting

All included hospitals have implemented CPOE [10] and BCMA systems. They use a variety of software packages, both for the CPOE and for the BCMA systems. As a consequence, procedures for prescribing and medication administration differ between hospitals. Table 1 summarizes the main characteristics. Medication administration procedures within a hospital vary slightly between wards because of differences in patient groups or tasks (eg, in some hospitals, short stay surgical patients do not wear wristbands, but these are attached to the medication cart).

The included hospitals use bar code-labeled unit dose systems to distribute medication to inpatients. In the pharmacy departments, pharmacy technicians dispense bar coded medication for individual patients into trays labeled with the patient’s name and bar code. Trays are placed in medication carts in which they are then delivered to the wards once a day (or more frequently). Wards do not have ward-based medication stock (except for emergency medication). One of the selected hospitals uses so-called bedside assortment picking carts [29]. A cart contains all the medication commonly used on the ward. With this system, nurses select the medication for administration during the medication administration rounds.

In general, there are 4 scheduled medication administration rounds in the participating hospitals: 6-10 AM, 10-2 PM, 6-8 PM, and 8-10 PM. Medications are administered by 1 nurse. Nurse trainees are supervised by registered nurses. In the participating hospitals, there are approximately 10-20 inpatients admitted on a ward served by a registered nurse and a nurse trainee. A large ward is split into smaller units each serving 10-20 inpatients, each aided by a registered nurse and a nurse trainee.

During a drug administration round, nurses select the prescribed medication for each inpatient from the prefilled trays or from the bedside assortment picking carts. In addition to the cart, nurses also take along the computer on wheels or the workstation on wheels to access the CPOE system during the drug administration round.

Inpatients do not use their own (out-of-hospital prescribed) drugs.

### Participants

The study will enroll patients admitted to the internal medicine and surgical wards of 4 Dutch hospitals in which a BCMA system is used to administer medication. To be eligible to participate in this study, a participant must meet the following criteria: be a hospitalized patient and receive medication on those nursing wards that are participating in this study. We will exclude patients younger than 18 years.

### Outcome Measures

The primary outcome measure of the study is the proportion of medication administrations with 1 or more MAEs. For this outcome, we will study the association between the MAE and the occurrence of 1 or more workarounds.

The secondary outcomes are the frequency and type of workarounds, the frequency and type of MAEs in the BCMA process, and the association of potential risk factors with workarounds.

**Table 1 table1:** Characteristics of the medication administration systems in the participating hospitals.

Item	Hospital 1	Hospital 2	Hospital 3	Hospital 4
Software system	RH Dharma	ViPharma	Klinicom	Pharma
System screen layout	Fixed layout	Fixed layout	Fixed layout	User-controlled screen layout
Administration system	Bedside assortment picking cart	Cart with prefilled patient-labeled trays	Cart with prefilled patient-labeled trays	Cart with prefilled patient-labeled trays
Log-in procedure for nurse	Once; automatic log-out after 15 minutes of inactivity	Once for 1 session	Once for 1 session	Once for 1 session
Log-out procedure for nurse	Manual; automatic log-out after 15 minutes of inactivity	Manual	Manual	Manual
Built-in additional check by nurse’s colleagues	Extra log-in for another nurse built in	Not possible	Extra log-in for another nurse built in	Not described in the instructions
Signal/alert system	Scanner beep and scanner warning light	Computer beep	Computer beep	Computer beep
Patient has no bar code	Not described in the instructions	Manual patient selection	Manual patient selection	Manual patient selection
Patient selection per administration round	Once, by selection of patient; automatically deselected after all medication for that round is administered	Twice, by selection and active deselection of patient after medication administration	Once, by selection of patient; automatic deselection after all medication for that round is administered	Once, by selection of patient; automatic deselection after all medication for that round is administered
Medication in the cart has no bar code	Robot-packed bar coded medication ordered from pharmacy	Manual drug selection	Manual drug selection	Nurse can overrule the system using her or his access code and manually select drug
More than 1 unit of the same drug for the same time prescribed	Scanned once, then the number of tablets is manually adjusted	Every drug unit is scanned	Scanned once, then the number of tablets is manually adjusted	Scanned once; a pop-up appears asking for the other tablets to be scanned
Patient away or sleeping	Prescribed medication is placed at the patients’ bedside, registered as given, and checked at 2:00 AM	Medication not given and not registered; noted in memo field	Medication not given and not registered; noted in memo field	Not described in the instructions
One-half or one-quarter of a tablet prescribed	Tablet scanned, plus code “half” or “quarter” scanned on computer	Not described in the instructions	Tablet scanned, plus noted by nurse in memo field on the screen	Not described in the instructions
Instructions on screen for nurse from pharmacy or prescriber	On-screen memo field included (medication data level)	On-screen memo field included (patient data level)	On-screen memo field included (medication data level)	On-screen memo field included (medication data level)

We will collect the following potential risk factors for workarounds using a structured data collection form (Multimedia Appendix 1): nurses’ characteristics (experienced, trained, or student nurse; nurses’ satisfaction with BCMA), workload characteristics (number of nurses on the ward, number of patients served by that ward, number of medicines per round per patient, number of medicines for all patients per round per ward), BCMA system characteristics (time after implementation of BCMA system on that ward, bar code on medication unit dose), medication characteristics (Anatomical Therapeutic Chemical Classification System [ATC] code of the medication, drug administration route), and general characteristics (hospital type, ward type, time of ward round, patient age and sex). We will ask the supervisor of the ward for data on the nurses’ education and experience. We will extract the number of patients on the ward, the medication and ATC code, and the number of drugs to administer to each individual patient during the specific administration rounds from the CPOE system. We will ask the supervising hospital pharmacist for the other risk factors.

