### Definitions and Classification

Workarounds are defined as “informal temporary practices for handling exceptions to normal workflow” for that specific ward and are operationalized as deviations from the available protocols [24]. Figure 1 depicts the BCMA workflow and the potential risk factors for workarounds in the BCMA process. We will classify workarounds using a self-developed classification system (Table 2) derived from the system of Koppel et al [26]. Workarounds can be related to patient identification, the scanning process, the alert signals, and other procedures, or can be work related. Allan and Barker [41] defined MAEs as “the administration of a dose of medication that deviates from the prescription as written (or ordered by CPOE) on the patient medication chart, or from standard hospital policy and procedures.” We will compare drug administrations with the doctor’s prescriptions as noted in the CPOE system in the pharmacy database. We will exclude intravenous and nonintravenous preparation errors because these errors are not preventable by BCMA and are thus unlikely to be influenced by workarounds in the BCMA process. We will classify the MAEs using the classification of van den Bemt et al [42] (Table 3). We will divide the number of erroneous medication administrations (containing 1 or more errors) by the number of observed drug administrations plus the number of omissions, thus using the concept of opportunities for errors as in other MAE research [43].

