**Figure 1 figure1:**
[figure not shown]
Flowchart of the bar code-assisted medication administration (BCMA) process in hospitals.

**Table 2 table2:** Classification of workarounds in the bar code-assisted medication administration process^a^.

Workaround type	Example workaround
Procedure related: standard operating procedure, or procedure unclear or unknown	Nothing scanned
Patient related: no patient wristband or patient not in the room	Bed scanned, or loose wristband scanned, patient unscanned
Medication related: medication not bar coded	Unscanned, unidentified medication given
Nurse related: nurse disturbed	Nurse forgets patient or gives medication twice
Computer or scanner related: computer or scanner down or broken	Signals or alerts unseen, unscanned medication given
Other workarounds	Medication scanned for multiple patients; half tablets scanned as full dose

^a^Derived from Koppel et al [26].

**Table 3 table3:** The most basic characterization of medication administration errors (MAEs)^a^.

MAE type	Example MAE
Omission	Drug prescribed, but not administered
Unordered drug administration	Drug administered, but not prescribed
Wrong dosage form	Drug dosage form administered to the patient deviating from prescribed dosage form: solution as an alternative to tablet
Wrong route of administration	Drug given by a wrong route of administration: oral liquid administered intravenously
Wrong administration technique	Drug administered using a wrong technique: intravenous push instead of intravenous infusion
Wrong dosage	Drug dosage too high or low: 20 mg instead of 20 μg
Wrong time of administration	Drug given at least 60 minutes too early or too late

^a^From van den Bemt et al [42].

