### Statistical Analysis

Data will be analyzed using IBM SPSS Statistics version 22 (IBM Corporation). We will analyze the potential association between workarounds and the occurrence of MAEs using univariate multilevel logistic regression, with the proportion of medication administrations with 1 or more errors as the dependent variable and the occurrence of workarounds as the independent variable. The nurse and the patient will be the levels in the multilevel analysis. We will analyze the occurrence of workarounds as a categorical variable, with the following categories: no workarounds (reference category), 1 workaround, 2 workarounds, and 3 or more workarounds. We will adjust for potential confounders by using multivariate multilevel logistic regression. The parameters in the multivariate multilevel logistic regression model will be hospital, ward type, day of the week, time schedule of medication administration rounds, ATC code, the number of drugs per patient per round, and the route of administration. We will report the adjusted odds ratio and 95% confidence interval. For the frequency and type of workarounds and MAEs, we will use descriptive statistics. Univariate and multivariate logistic regression will determine the association of the risk factors with the workarounds.

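### Bar-code status is tested as a risk factor for workarounds, yet one of the six workaround types can occur only on doses without a bar code, so part of the pooled odds ratio is built in

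*Protocol article*

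**What the plan says.** All references are to the Protocol article.

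- **Predictor.** Outcome Measures lists the potential risk factors for workarounds, including "BCMA system characteristics (time after implementation of BCMA system on that ward, bar code on medication unit dose".
- **Outcome definition.** Under Definitions and Classification, workarounds "are operationalized as deviations from the available protocols". Data Collection says they are found by comparing the observation record with the ward's own procedures.
- **Outcome classification.** Table 2 sorts workarounds into six types. One is "Medication related: medication not bar coded", with the example "Unscanned, unidentified medication given".
- **Local rules.** For medication in the cart without a bar code, Table 1 gives "Robot-packed bar coded medication ordered from pharmacy" for Hospital 1, "Manual drug selection" for Hospitals 2 and 3, and "Nurse can overrule the system using her or his access code and manually select drug" for Hospital 4.
- **Analysis.** Statistical Analysis says "Univariate and multivariate logistic regression will determine the association of the risk factors with the workarounds". It neither sets the overlapping type apart nor lists the covariates of this multivariable model.

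**The concern.** A risk factor should be measured separately from the outcome it is meant to explain. Here one outcome type carries the predictor's value in its label: it can be recorded when the bar code is missing and cannot be recorded otherwise. Every case of that type adds to the association between a missing bar code and any workaround, whether or not nurses behave differently with such doses.

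The hospital procedures add a second layer. The same act, giving an uncoded dose, departs from the stated route in one hospital and can follow it in the other three. A pooled odds ratio averages over these rules.

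The stake is the secondary objective. The abstract says that knowledge of determinants should guide a focused effort to reduce workarounds. If bar-code status came out as a leading determinant, a reader could not tell how much was a finding and how much came from the classification.

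**Working it through.** The plan states no figure for this association, so there is none to reproduce. The check sets the sections side by side and then illustrates the possible size.

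**Step 1: which workarounds are open to which doses**

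| | Dose with bar code | Dose without bar code |
|---|---|---|
| Table 2 type for uncoded medication | impossible | possible |
| Leaving a scannable drug unscanned | possible | impossible |
| Patient-identification and other types | possible | possible |

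The first row pushes the odds ratio for a missing bar code up, and the second pushes it down. Only the third row compares like with like.

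**Step 2: what the hospital procedures imply**

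| Hospital | Table 1 route for uncoded medication | Giving the uncoded dose by manual selection |
|---|---|---|
| 1 | bar-coded product ordered from pharmacy | on a plain reading, departs from the route |
| 2 and 3 | manual selection | follows the route |
| 4 | override by access code, then manual selection | follows the route if the override is used |

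**Step 3: possible size**

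Inputs:
- Overall workaround rate w = 8%, the assumption in Sample Size Calculation.
- Share of doses without a bar code, s = 2%, 5% or 10%. The document gives no figure, so this is assumed.
- Proportion of uncoded doses classed as workarounds, q. Also assumed, and varied over its range.

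Formulas:
- Rate in bar-coded doses: r = (w − s·q)/(1 − s)
- Odds ratio, no bar code versus bar code: [q/(1 − q)] / [r/(1 − r)]
- Share of all workarounds that come from uncoded doses: s·q/w

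Example with s = 5% and q = 50%: r = (0.08 − 0.025)/0.95 = 0.0579, odds ratio = 1/(0.0579/0.9421) = 16.3, share = 0.025/0.08 = 31%.

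| q | OR, s = 2% | OR, s = 5% | OR, s = 10% | Share of workarounds, s = 5% |
|---|---|---|---|---|
| 8% | 1.0 | 1.0 | 1.0 | 5% |
| 25% | 4.0 | 4.4 | 5.1 | 16% |
| 50% | 13 | 16 | 29 | 31% |
| 90% | 133 | 235 | not possible | 56% |
| 100% | infinite | infinite | not possible | 62.5% |

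The two impossible cells would need more workarounds than the 8% total (for example 0.10 × 0.90 = 9%).

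The odds ratio can also fall below 1. If manual selection is compliant and uncoded doses show workarounds at half the overall rate (q = 4%, s = 5%), then r = (0.08 − 0.002)/0.95 = 0.0821 and the odds ratio is (0.04/0.96)/(0.0821/0.9179) = 0.47.

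Taking 8% as the rate in bar-coded doses alone gives (0.5/0.5)/(0.08/0.92) = 11.5 at q = 50% and (0.9/0.1)/(0.08/0.92) = 103.5 at q = 90%. With s = 5% and q = 90% this implies 0.05 × 0.9 + 0.95 × 0.08 = 12.1% overall, above the protocol's 8%, so the table above is the more consistent illustration.

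**Step 4: reading**

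The odds ratio depends heavily on q, and q depends in part on how Table 1, Table 2 and the definition are reconciled when doses are coded. It is wholly fixed by coding only at q = 100%, a rule the document does not state.

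**The case against.** A reader might infer that a missing bar code is part of the workaround definition, so that the odds ratio is simply the coding rule and the multivariable model is distorted. The document does not support that.

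- **Not the definition.** A workaround is a deviation from ward procedure. The missing bar code labels the cause of one type out of six, and the example under it is a nurse's action.
- **Neither sufficient nor necessary.** Table 1 gives a route for uncoded medication in all four hospitals, so such a dose can be handled without deviating. A nurse can also truly deviate with one, by skipping the manual selection or the override, or in Hospital 1 by giving it anyway. Bar-coded doses have workarounds of their own.
- **Distortion of other coefficients is not shown.** The covariates of the risk-factor model are not listed. Harm to the other estimates would need correlation with bar-code status (ATC code, route and hospital are plausible) or near-complete separation.
- **A legitimate determinant.** A missing bar code is a process barrier that a pharmacy can act on. Dropping it, or fitting the only model on bar-coded doses, would answer a different question.
- **Unseen detail.** The recording forms are in multimedia appendices that are not shown and may hold coding rules.

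All of this stands against the strong reading. It does not remove the overlap: the type exists only at one level of the predictor, and the stated analysis does not separate it. The Hospital 1 route also cuts both ways. It leaves room for real deviation, but it makes the same act count there and not necessarily elsewhere.

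**Conclusion.** The point holds in limited form. Bar-code status and one of the six workaround types overlap by construction, and hospital procedure affects whether giving an uncoded dose can count as a deviation at all. A pooled odds ratio of any workaround on bar-code status is therefore partly built in.

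The size of that part is unknown. The illustrative values, from below 1 to above 200, rest on assumed shares of uncoded doses and assumed coding proportions. They show sensitivity to the coding rule and are not an estimate of bias.

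The consequence is confined to the secondary aim on determinants. Bar-code status is not among the adjustment variables listed for the primary model of workarounds and administration errors. The change is still worth making, because it is cheap and the result is meant to guide practice.

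**What to change.** Keep bar-code status as a candidate determinant and add three things.

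1. **Second estimate for this factor.** Report the bar-code odds ratio also with the overlapping Table 2 type removed from the outcome, so that a dose whose only workaround is of that type counts as having none. Beside it, give by hospital the number of uncoded doses and how they were handled. Note that uncoded doses still cannot have a drug left unscanned in breach of procedure, so this estimate may lean downward.
2. **One clarifying sentence.** State that an uncoded dose handled by the ward's own procedure is not a workaround on that point, in line with the definition. Other deviations on the same dose still count.
3. **Sensitivity model.** Refit the model for the other risk factors on bar-coded doses only, without the bar-code term, and compare coefficients. This tests the possible distortion directly.

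Bar-code status, workaround type and hospital are already to be collected, so no new data are needed. The cost is a little extra analysis and slightly fewer doses in the sensitivity model. If type has not been recorded for each workaround on a dose, the first item would need the observation forms to be checked.
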